ProMES is a comprehensive productivity improvement approach firmly grounded in motivational theory [24, 25] and performance measurement. It utilizes diagnostic measurement to optimize the effectiveness and performance of people in complex organizations. ProMES is designed with implementation in mind: incumbents of a given work unit, supervisors, and upper level management will engage in the development of measures for capturing each important aspect of their daily work (in this case coordination). Through a facilitated process, these measures are defined, weighted, and prioritized in order to create indicators of both overall effectiveness and specific aspects of daily work. Moreover, ProMES helps address all three of Okhuysen and Bechky’s integrating conditions of coordination. The process of identifying objectives helps clarify expectations (plans and rules), which helps improve shared understanding among PACT members; the process of developing indicators and contingencies helps clarify roles and routines (thereby improving predictability and accountability) by making expectations clear, thus requiring team members to think about what they need to perform to standard.

Previous research in intensive care unit and mental health care settings has shown that successful use of ProMES can improve efficiency and quality of care. For example, in studies conducted with a German mental health hospital the ProMES methodology was utilized across organizational levels for the top management team, samples of nurses, and three samples of technicians. Results indicated that overall productivity scores for participating units were, on average, 0.78 standard deviations higher after implementation [23].

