### Participants

For this phase, we will recruit members of all available PACTs at the four Network 12 study sites. Given our site selection criteria, we estimate each study arm will have an average of approximately 152 members clustered into 28 PACTs. For purposes of informed consent, we will treat all PACT members at a site as study subjects; we are aware that not all PACT members may consent to participate; however, our intervention is an intent-to-treat design, and the unit of analysis is the PACT, not the individual PACT member (our outcome of interest, coordination, is by definition a collective construct). Consequently, as long as at least the provider of a given PACT consents, we will include that PACT’s data in our analyses, taking into consideration the limitations of that PACT’s data.

Optimal design software developed by Raudenbush and colleagues [28] was used to calculate the estimated effect size for varying levels of power for a multilevel cluster randomized trial with repeated measures. With a two-tailed alpha of 0.05 and 6 sites with an average of 10 PACTs per site, an intra-class correlation coefficient for sites of 0.02 (estimated from prior VA data), and approximately 12 repeated assessments, we have 80 % power to detect a medium-to-large effect size (*δ* = 1.13) and 87 % power to detect a large effect (*δ* = 1.25). Pritchard and colleagues’ [19] meta-analysis examining the effectiveness of ProMES as improving productivity found a large overall effect size (*δ* = 1.44); accounting for moderators, effect sizes were as high as 2.21. Thus, we should be able to adequately detect improvements using the proposed number of PACTs.

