### Data analysis

For each objective, we will create composite score of coordination effectiveness, calculated per ProMES recommendations, as the simple sum of all the indicators relevant to that objective. The unit of analysis will be the PACT. We will compare across arms the improvement in coordination effectiveness score over time (baseline vs. performance periods) using growth curve modeling. Coordination effectiveness would be the dependent variable; time point and study arm would be level 1 and 2 predictors, respectively. Each will be modeled separately. A significant, positive main effect of time and study arm will indicate differential improvement across arms over time; an intervention arm slope that is significantly steeper than the control arm indicates support for our hypothesis. In addition to our planned hypothesis test, we also have the opportunity to investigate the extent to which performance on existing care coordination measures is a function of PACT coordination effectiveness. We will conduct separate analyses for each care coordination measure in the PACT Compass. For each, we will test a growth curve model with Compass measure as the dependent variable and time, study arm, and the coordination effectiveness composites as predictors. A significant, positive main effect of coordination effectiveness after accounting for time and study arm would indicate support for the hypothesis that better PACT coordination behaviors is associated with better care coordination outcomes as currently measured by the PACT Compass.

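### The unqualified claim of adequate power rests on an effect of 1.44 and passes over the 0.78 SD health-care effect the protocol itself cites, at which the stated inputs give only about 50% power

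*Protocol article*

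**What the plan says.** Under Phase 3, Participants, the power calculation is for a multilevel cluster randomized trial with repeated measures. Its starting point is "With a two-tailed alpha of 0.05 and 6 sites with an average of 10 PACTs per site". The site-level ICC is set at 0.02 on the basis of earlier VA data, and each PACT is assessed about 12 times. The result is "we have 80 % power to detect a medium-to-large effect size (*δ* = 1.13"), with 87% power at δ = 1.25. The paragraph then cites a meta-analysis of ProMES with an overall effect of 1.44, and up to 2.21 once moderators are considered, and concludes: "Thus, we should be able to adequately detect improvements using the proposed number of PACTs".

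In Phase 1, Overview of ProMES methodology, the article argues that ProMES works in health care and gives one numerical example, from a German mental health hospital: "overall productivity scores for participating units were, on average, 0.78 standard deviations higher after implementation".

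In Phase 3, Data analysis, the hypothesis is tested between arms: "an intervention arm slope that is significantly steeper than the control arm indicates support for our hypothesis".

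Phase 3, Design and site selection, names four facilities. Participants expects 28 PACTs in each arm. Trial status adds that controls are now a random sample of PACTs from anywhere in the network.

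**The concern.** The article uses 0.78 SD to show that the method works in health care, and a figure nearly twice as large (1.44 / 0.78 = 1.85) to show that the sample is big enough. The smaller figure is 1 − 0.78/1.13 = 31% below the effect detectable with 80% power, and the sample-size paragraph does not discuss it. Describing 1.13 as medium-to-large also makes the detectable effect sound more modest than it is, since it exceeds the effect the article cites from a hospital.

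At stake is how far the power statement can be relied on. If the feedback works in PACTs about as well as in that hospital, the study may have only an even chance of showing it, and a reader of the adequacy sentence would not know this.

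**Working it through.** **Inputs.** From Phase 3, Participants: two-sided α = 0.05, J = 6 sites, n = 10 PACTs per site, ICC ρ = 0.02, about 12 assessments, 80% power at 1.13, 87% at 1.25, comparison effect 1.44. From Phase 1, Overview of ProMES methodology: 0.78 SD. The variance of the repeated measurements is not stated.

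**Formula.** For a two-arm comparison with sites as clusters, SE = √{4[ρ + (1 − ρ)/n]/J}, noncentrality = δ/SE, and df = J − 2. Power comes from the noncentral t distribution.

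**Step 1: the protocol's own figures.** With J = 6 and n = 10:
- ρ + (1 − ρ)/n = 0.02 + 0.098 = 0.118
- SE = √(4 × 0.118/6) = 0.280, df = 4
- Power = 84.8% at 1.13 and 90.7% at 1.25

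These are 4 to 5 points above the printed values. A shortfall of this kind is what measurement error in the repeated assessments would produce: an added error variance of about 0.17 at PACT level gives 80.0% and 86.8%. Because the protocol does not state that variance, the printed figures cannot be reproduced outright.

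**Step 2: calibrate to the printed power.** With 4 df, 80% power needs a noncentrality of 3.761, so the implied SE = 1.13/3.761 = 0.300. At 1.25 this gives 86.8%, matching the printed 87%. The two printed points agree with each other.

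**Step 3: power at the cited effects.**

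| Effect (SD) | Calibrated to printed power, 4 df | Direct, 6 sites × 10 PACTs | Illustration, 4 sites × 14 PACTs |
|---|---|---|---|
| 0.78 | 50.5% | 55.8% | 31.7% |
| 1.13 | 80.0% | 84.8% | 52.4% |
| 1.25 | 86.8% | 90.7% | 59.2% |
| 1.44 | 94.0% | 96.3% | 69.1% |

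The calibrated figure at 0.78 depends little on the degrees of freedom: 54.8% with 2 df, 49.9% with 5, 49.2% with 10 and 49.0% with 58.

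**Step 4: the design as described.** The last column spreads 28 PACTs per arm over two sites per arm: 0.02 + 0.98/14 = 0.090, SE = √(4 × 0.090/4) = 0.300, df = 2. It is an illustration only, because the control PACTs are now to be sampled across the whole network and the clustering is no longer four equal sites. It shows that the six-site figures are not pessimistic.

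**The case against.** Planning on a meta-analytic estimate is an ordinary and defensible choice, and the printed 80% and 87% are consistent with each other. Both points stand: this is not a calculation error.

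The 0.78 is introduced as an example. It is a before-after change without controls in one mental health hospital, and the article does not offer it as a planning value for primary care. That also stands, so it cannot be called the expected effect here. But since the hypothesis is tested against a control arm, any improvement that controls also show would be subtracted from it.

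The scales may differ. Nothing shows that 0.78 and the δ of a repeated-measures cluster design share a standard deviation. If 0.78 were in units of the single-assessment SD and the 12 assessments were averaged, power could be higher: about 75% if PACTs account for 0.49 of the variance. That model, however, gives 96% at 1.13 and so contradicts the printed 80%. The protocol does not show a common scale for 1.44 either; if comparability fails, the adequacy sentence loses its support too.

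Two stronger readings are tempting. A reader might infer that 1.44 comes from outside health care; the article does not say which settings the meta-analysis covers. A reader might also infer that a null result would be taken as proof that feedback does not work; the Data analysis section says only what would support the hypothesis.

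**Conclusion.** The concern holds as a point about an unqualified conclusion. Under the stated six-site inputs, power reaches 80% only for effects of about 1.1 SD or more. At the 0.78 SD cited from health care it is about 50% (50.5% calibrated, 55.8% direct), provided 0.78 is on the scale of δ.

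The six-site inputs are themselves in conflict with the four sites and 28 PACTs per arm. Under the four-site illustration power is about 32% at 0.78, and even at the effect chosen to justify the sample it is 69%. The 50% should therefore not be quoted as the power of the trial as run. What the documents support is that adequacy depends on an effect well above the one health-care figure they cite, and that the article does not say so.

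**What to change.** In Phase 3, Participants:

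1. Recompute power for the design actually run, including the number of sites, the PACTs per arm and the network-wide control sample, and state the repeated-measures variance assumed.
2. Report power at 0.78 beside 1.13, 1.25 and 1.44. State that this treats all of them as being on one SD scale, and that 0.78 is an uncontrolled before-after change.
3. Drop the medium-to-large label for 1.13.
4. Replace the adequacy sentence with one on these lines: under the stated six-site inputs, power is adequate only for effects of about 1.1 SD or more, and is about one half or lower at the 0.78 SD cited from a health-care setting. Update the figures once item 1 is done.

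This costs one recalculation and some rewording, with no added sites or PACTs. The downside is a less favourable power statement.

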### Procedures

#### Begin measuring coordination

Assessment of change requires a baseline; consequently, we will use the time period between completion of phase 1 and completion of phase 2 to passively monitor coordination at all study sites.

#### Identify point-of-care aids

The performance period will begin upon final approval by leadership of the point-of-care aid recommendations document.

#### Provide periodic and feedback

We will provide monthly audit and feedback reports on the PACTs’ coordination performance (as measured by the indicators developed in phase 1) to all PACTs in the intervention arm. We will use standardized, ProMES-based audit and feedback reports as a starting point [29]. We will work with our Network 12 partners to adapt reports to their needs based on their suggestions and what research has shown to maximize feedback effectiveness [26, 27].

These reports will be utilized in feedback meetings between the PACT Teams and the PACT Team Leader to identify barriers and facilitators to productivity and discuss strategies to implement needed change. PACT Team Leaders will be trained on how to run these feedback meetings. Training will include interpretation of the feedback report, as well as instruction on delivering feedback in a team setting and discussing the results with the PACTs. Previous research suggests monthly feedback meetings constitute an appropriate time interval for providing face-to-face feedback of this sort [19]. We will therefore suggest monthly feedback meetings, adjusting this frequency interval based on the feedback needs of the PACT and availability of indicator data.

#### Adjust system as necessary

Three months after the performance period begins, the design and advisory teams will review the point-of-care aids, providing suggestions for adjustments. The design and research teams will collect suggestions and convene for two 2-h meetings to make adjustments as needed. Coordination will then be monitored from that point forward using the revised point-of-care aids.

### Measures

#### Coordination

Coordination will be assessed using the measures developed in phase 1. In addition, the contingency process enables us to form an overall care coordination composite, defined as the simple sum of the indicators [23]. No weighting or additional transformations are necessary, as nonlinearity and complexities are accounted for in the indicators’ contingencies (i.e., the transformation from raw score to an effectiveness scale).

#### Care coordination

In addition to the ProMES-developed care coordination measures, we will also monitor existing care coordination measures in the PACT Compass (VA’s dashboard for reporting a variety of quality, safety, and value measures related to PACTs) for each study site. As of this writing, these measures consist of the following: ER/Urgent Care Utilization Rate by Panel, Inpatient Admission Rate, 2-day contact post-discharge ratio, and 7-day contact post-discharge ratio. With both standard measures of care coordination and the ProMES-developed measures of coordination in hand, it will be possible to discern the extent to which the values of these existing measures of care coordination are contingent upon coordination behaviors among PACT members. We will also be able to compare agreement between measures of coordination and standard process measures currently in use.

### Data analysis

For each objective, we will create composite score of coordination effectiveness, calculated per ProMES recommendations, as the simple sum of all the indicators relevant to that objective. The unit of analysis will be the PACT. We will compare across arms the improvement in coordination effectiveness score over time (baseline vs. performance periods) using growth curve modeling. Coordination effectiveness would be the dependent variable; time point and study arm would be level 1 and 2 predictors, respectively. Each will be modeled separately. A significant, positive main effect of time and study arm will indicate differential improvement across arms over time; an intervention arm slope that is significantly steeper than the control arm indicates support for our hypothesis. In addition to our planned hypothesis test, we also have the opportunity to investigate the extent to which performance on existing care coordination measures is a function of PACT coordination effectiveness. We will conduct separate analyses for each care coordination measure in the PACT Compass. For each, we will test a growth curve model with Compass measure as the dependent variable and time, study arm, and the coordination effectiveness composites as predictors. A significant, positive main effect of coordination effectiveness after accounting for time and study arm would indicate support for the hypothesis that better PACT coordination behaviors is associated with better care coordination outcomes as currently measured by the PACT Compass.

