### Objectives

Guided by Okhuysen and Bechky’s coordination framework [7], “this project’s objective is to determine the point-of-care information needs of PACT members to successfully coordinate care and to identify the optimal mechanisms of delivering that information at the point-of- care*.*” We define point of care in the PACT context as any setting where a provider evaluates clinical information and makes a healthcare decision. This broad definition encompasses both traditional face-to-face encounters at clinical visits as well as non face-to-face interactions (e.g., telephone calls, secure messaging, or processing information from the electronic medical record) that are integral to PACT care delivery.

To accomplish our objective, we will employ the Productivity Measurement and Enhancement System (ProMES) to systematically identify organizational objectives and develop clear, accountable measures of coordination, which in turn will help identify care coordination needs in PACT settings. ProMES is a performance measure development method from I/O psychology rooted in 30 years of empirical and theoretical work in motivation, feedback, participation in decision making, and goal setting [19, 20]. ProMES uses specific criteria for evaluating measure quality, including several criteria used by the National Quality Forum (see Additional file 1). Via this methodology, we will accomplish the following:Develop measurable criteria for effective coordination in PACTs, prioritized and weighted by contribution to overall quality of care.Use the measurable criteria developed in Aim 1 to identify the specific information needed at the point of care to improve coordination and recommend point-of-care aids for delivering the needed information.Assess the effect of adopting the aforementioned coordination criteria and feedback on PACT clinicians’ coordination behaviors. Our hypothesis:*H*_1_—Coordination behaviors at sites adopting measurable criteria and feedback will be significantly more effective than coordination behaviors at control sites.

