### Step 1: identify care coordination objectives

The design team will be led by facilitators in a 1-day exercise to identify care coordination objectives (see Table 2 for examples). Objectives will be defined by design team members in the context of PACTs coordinating care for the three conditions of interest. For each clinical condition, the design team is charged with answering, “what is the PACT trying to accomplish when coordinating care?” Trained facilitators will guide the design team to arrive at three to six objectives that meet six recommended criteria ([23]; see also Additional file 1). Objectives will be compared against these criteria to ensure their utility in subsequent steps.

**Table 2 Tab2:** Sample potential coordination objectives and indicators resulting from ProMES methodology

Objective	Indicator
1. Optimize balance of quality vs. length of life given patient preferences	1. Score on patient preferences/satisfaction survey
	2. Length of life compared to algorithm based on stages of disease
2. Ensure timely screening, delivery, and follow-up of care	3. Mean number of days between date provider orders test and date clerk schedules appointment with the patient
	4. Percent of patients eligible for screening tests who receive them in the specified period.
	5. Percent of patients eligible for diagnostic tests who receive them in the specified period.
3. Ensure care is evidence-based and comprehensive by providing the right expertise mix to care for patient	6. Percent of provider type match per patient problem, i.e., the correct type of provider should be working on a patient for every problem on the patient problem list

Sample objectives and indicators are from a brief pilot ProMES session conducted for care coordination specific to cancer care.

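### One directional hypothesis is tied to three to six separately modelled objective composites, with no primary composite, no rule for mixed results and no model for the overall composite

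*Protocol article*

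**What the plan says.** The Objectives section of the protocol article gives one hypothesis, H1, with a direction: "Coordination behaviors at sites adopting measurable criteria and feedback will be significantly more effective than coordination behaviors at control sites".

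Step 1 of Phase 1 sets the number of objectives: "Trained facilitators will guide the design team to arrive at three to six objectives that meet six recommended criteria". The sentence before it opens with "For each clinical condition, the design team is charged with answering", so it is not fully clear whether the target applies once or to each of the three conditions.

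The Coordination paragraph under Phase 3 Measures says that "the contingency process enables us to form an overall care coordination composite, defined as the simple sum of the indicators". Step 3 of Phase 1 prepares for this by putting all indicators on a common scale so that they can be combined into one measure.

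The Phase 3 Data analysis section works objective by objective: "we will create composite score of coordination effectiveness, calculated per ProMES recommendations, as the simple sum of all the indicators relevant to that objective". After listing time point and study arm as predictors, it adds: "Each will be modeled separately". It counts a significantly steeper slope in the intervention arm as support for the hypothesis, and refers to the planned hypothesis test in the singular. It does not name the overall composite.

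The only significance level in the article, a two-tailed 0.05, stands in the power calculation (Phase 3 Participants), which describes a single comparison.

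**The concern.** The article commits to one hypothesis and one test, but the analysis it describes produces several tests. If two of five objective composites show a steeper intervention slope, a reader cannot tell from the text whether H1 is supported. If one success is enough, the chance of wrongly declaring support exceeds that of a single test. If all must succeed, power falls below what was planned for one comparison. The measure that would give a single answer, the overall composite, is defined but has no place in the analysis.

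This goes beyond a detail left for an analysis plan. The article itself fixes the outcomes, the separate modelling and the criterion for support, and these do not fit its own singular hypothesis and test.

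**Working it through.** **The plan's own figure.** The article states no overall error rate for H1. It states power of 80% at δ = 1.13 and 87% at δ = 1.25, for 6 sites, 10 PACTs per site, intra-class correlation 0.02 and two-tailed 0.05. A simple site-level F test has non-centrality λ = Jδ² / [4(ρ + (1−ρ)/n)] on J − 2 = 4 df. At δ = 1.13, λ = 6 × 1.2769 / (4 × 0.118) = 16.2, which gives 84.8%. At δ = 1.25, λ = 9.375 / 0.472 = 19.9, which gives 90.7%. The variance components for the repeated measures are not given, so an exact match is not possible. The two stated values do agree with each other: on 4 df, 80% at 1.13 implies 86.8% at 1.25. Both are figures for one test.

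**Inputs for the error rate**
- Number of composites k: 3 to 6 (Step 1).
- Level per model: two-sided 0.05. This is an assumption, carried over from the power calculation.
- Decision rule: any one favourable result supports H1. This is an assumption; no rule is written.
- Direction: only a steeper intervention slope supports H1, so the false-support rate per test is 0.05 / 2 = 0.025.

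**Independent tests**

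False support = 1 − 0.975^k. Any false significant arm difference, in either direction = 1 − 0.95^k.

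| k | False support for H1 | Either direction |
|---|---|---|
| 1 | 2.5% | 5.0% |
| 3 | 1 − 0.9269 = 7.3% | 1 − 0.8574 = 14.3% |
| 4 | 9.6% | 18.5% |
| 5 | 11.9% | 22.6% |
| 6 | 1 − 0.8591 = 14.1% | 1 − 0.7351 = 26.5% |

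**Correlated tests.** The composites come from the same PACTs over the same months, so positive correlation is likely. The article gives no value, so a range is shown. It comes from simulating equally correlated normal test statistics (500,000 draws, cut-off 1.96).

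| Correlation | False support, k = 3 | False support, k = 6 | Either direction, k = 3 | Either direction, k = 6 |
|---|---|---|---|---|
| 0.3 | 6.8% | 12.2% | 13.5% | 24.1% |
| 0.5 | 6.3% | 10.3% | 12.6% | 20.7% |
| 0.7 | 5.4% | 8.2% | 10.9% | 16.4% |
| 0.9 | 4.2% | 5.4% | 8.3% | 10.9% |

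**If the target applied to each of three conditions** (one possible reading, not stated), k would be 9 to 18, and false support under independence would be 20.4% to 36.6%.

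**Power after Bonferroni adjustment.** Take the stated 80% at δ = 1.13 as an F test on 4 df (an assumption; λ = 14.15). Bonferroni levels of 0.05/3 = 0.0167 and 0.05/6 = 0.0083 then give a power per composite of about 52% and 35%.

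**The case against.** The strongest reply is that this is a condensed journal article, and that the level per test, the multiplicity method and the handling of mixed results usually belong in an analysis plan that is not shown. For those details taken alone, the reply stands. It does not remove the mismatch within the article between one hypothesis, several separately modelled outcomes and an overall composite without a model.

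Four further limits are fair:

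- A reader might infer up to 26% false support. The documents do not bear that out. The figure is the chance of a false significant difference in either direction, with six independent tests. A significantly worse intervention slope cannot support H1, so the corresponding figure is 14.1%, and lower with positive correlation.
- A reader might infer that the plan tests each composite at 0.05 and accepts any one success. Neither is written. The error rates are conditional on both.
- A reader might infer that the overall composite was created as the H1 outcome and then abandoned. The Measures text says only that it can be formed; it is never designated for H1. What can be said is that the Data analysis section does not name it.
- The subject of "Each will be modeled separately" is not explicit, and the sentence follows one about predictors. The per-objective reading is still the natural one. Modelling time and arm in separate models could not give the slope comparison the section relies on, and the section later refers to the composites in the plural.

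**Conclusion.** The point holds in this form. H1 is a single directional hypothesis with a single planned test, but the analysis models one composite per objective, names none as primary, gives no rule for mixed results and assigns no model to the overall composite.

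With two-sided 0.05 per model and an any-one-success reading, false support for H1 is about three times (k = 3: 7.3 / 2.5) to nearly six times (k = 6: 14.1 / 2.5) that of a single test under independence, and less with positive correlation. The number of objectives finally adopted is not shown, so the range for k rests on the stated target. That the outcome for H1 is unsettled does not depend on these assumptions; the size of the inflation does.

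**What to change.** In the Phase 3 Data analysis section, name the overall composite from the Measures section as the single primary outcome for H1, tested by the time-by-arm interaction at two-sided 0.05. Report the objective composites as secondary, with Holm adjustment, to show which objectives drive the result. This brings false support back to 2.5% and keeps the planned level.

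Alternatively, keep the objective composites as the H1 outcomes, adjust across them, and state how many must succeed for H1 to be supported. This also controls the error rate, but on the assumption shown above it costs considerable power per composite.

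The cost of the first option is wording only, with no new data. The Trial status section reports that the development meetings are complete and that Phase 3 is being prepared, so the choice can be fixed before the arms are compared. The downside is that an effect confined to one objective becomes a secondary finding.

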### Project description and study design

This project consists of three phases: (1) developing measurable, prioritized point-of-care criteria for effective PACT coordination, to be accomplished using ProMES (detailed below); (2) identifying the specific information needed at the point of care to improve coordination and recommend point-of-care aids for delivering the needed information, to be accomplished via focus groups with the phase 1 participants; and (3) assessing the effect of adopting the aforementioned coordination standards and point-of-care aids on PACT clinicians’ coordination behaviors.

Phase 3 consists of a trial with two arms: (1) a concurrent control arm drawn randomly from PACTs which will be monitored passively and (2) a measurement and feedback arm (two sites from a single regional network), which will be involved in designing the coordination measures and identifying the point-of-care aids and will receive periodic feedback on their coordination performance. The design of the three phases of the study is summarized in the flow chart in Fig. 1. Each phase is discussed below in detail.

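### The phase 3 analysis reads main effects of time and arm as differential improvement, and the time-by-arm term that its own slope criterion needs is never named

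*Protocol article*

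**What the plan says.** The protocol article's phase 3 Data analysis section sets the comparison: "We will compare across arms the improvement in coordination effectiveness score over time (baseline vs. performance periods) using growth curve modeling". The unit of analysis is the PACT, and the predictors are given as follows: "time point and study arm would be level 1 and 2 predictors, respectively". No product or cross-level term is named.

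One sentence then makes two interpretive statements, separated by a semicolon:

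- First: "A significant, positive main effect of time and study arm will indicate differential improvement across arms over time".
- Second: "an intervention arm slope that is significantly steeper than the control arm indicates support for our hypothesis".

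The Objectives section words H1 without reference to change over time: "Coordination behaviors at sites adopting measurable criteria and feedback will be significantly more effective than coordination behaviors at control sites".

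On the arms, Project description and study design makes the intervention arm two sites of one regional network, which also help to design the measures. Trial status says that the controls are now a random sample of PACTs from anywhere in the network.

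**The concern.** The first statement gives a rule for reading the trial's one planned hypothesis test, and the rule does not follow from the quantities it names. Differential improvement means that the change differs between arms. Neither a main effect of time nor a main effect of arm, nor the two together, measures that.

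The design makes the mistake matter. Random sampling of control PACTs is not random allocation to arms, and no such allocation is described, although the power paragraph refers to a cluster randomised design. Chosen sites may differ in level from PACTs sampled elsewhere before any feedback is given. The PACT model had only recently been introduced nationwide, so both arms may also drift upwards. A standing gap plus a shared trend is exactly the pattern that yields two positive main effects.

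At stake is a report of differential improvement that rests on the wrong coefficients. There is also a risk that the fitted model, if built literally from the listed predictors, contains nothing with which to test the slope criterion.

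**Working it through.** **1. What each coefficient means.** Write the score of PACT *i* at time *t*, with arm *A* (0 control, 1 intervention), as

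Y = b0 + b1·t + b2·A + b3·t·A + PACT random effects + error.

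The control slope is b1, the intervention slope is b1 + b3, and differential improvement is b3.

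- *Additive model, as the predictors are listed:* b3 is fixed at 0, so both arms share slope b1 by construction. The first statement asks for b1 > 0 and b2 > 0, which describes parallel rising lines. The second statement asks whether the slopes differ, and this model cannot answer that.
- *Model with the interaction:* b1 is the control arm's slope, and b2 is the gap at whatever point is coded t = 0. If that point is baseline, b2 is only the baseline gap. Positive b1 and b2 still say nothing about b3.

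The first statement is therefore wrong in either model, and the second needs b3.

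**2. The plan's own figures.** No stated figure bears on this point. The stated power (80% at δ = 1.13, 87% at δ = 1.25) cannot be rebuilt in its repeated-measures form, because the within-PACT and slope variances are not given.

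**3. Illustration.** From the protocol: 28 PACTs per arm, about 12 assessments, two-sided 0.05. Assumed, not in the documents: the variances, the arm gaps, linear change, an equal slope of 0.05 per month in both arms, and no clustering by site. Residual SD is 0.7 in both variance sets.

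- Set 1: PACT SD 1.0, slope SD 0.05 per month.
- Set 2: PACT SD 0.7, slope SD 0.03 per month.

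SD of a PACT mean = √(PACT SD² + 0.7²/12). SE of the arm difference = that SD × √(2/28).

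- Set 1: √(1 + 0.0408) = 1.020; SE = 1.020 × 0.267 = 0.273.
- Set 2: √(0.49 + 0.0408) = 0.729; SE = 0.729 × 0.267 = 0.195.

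The critical t on 54 df is 2.005. A noncentral t with noncentrality gap/SE gives the chance of a significant positive arm effect. The time effect is almost always significant here: its SE is √(slope SD² + 0.49/143)/√56, or 0.0103 and 0.0088, so 0.05/SE is 4.9 and 5.7. The arm effect therefore decides whether the main-effects reading is met.

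| Constant gap, equal slopes | Set 1: gap/SE | Set 1: formula | Set 1: simulated | Set 2: gap/SE | Set 2: formula | Set 2: simulated |
|---|---|---|---|---|---|---|
| 0.3 | 1.10 | 19% | 19% | 1.54 | 33% | 33% |
| 0.5 | 1.83 | 44% | 42% | 2.57 | 71% | 71% |
| 0.8 | 2.93 | 82% | 83% | 4.11 | 98% | 98% |

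The slope test in the same scenarios is significant in the favourable direction in about 2–3% (set 1) and 2.4–2.6% (set 2). The nominal value is 2.5%.

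**4. The converse, with slopes that truly diverge.**

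- Set 2, slopes 0 and 0.08 per month: the slope test is positive in about 99%. The main-effects reading is met in 2% when the arms' average levels coincide and in 60% when both start level.
- Set 1, a differential gain of 1.13 SD over the year: the slope test is positive in over 99%. The main-effects reading is met in 51% when the arms start equal and in 4% when the intervention arm starts 0.5 SD lower.

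**The case against.** The strongest reply is to read the sentence to its end. Its second half is the only part that mentions the hypothesis, and it ties support to a significantly steeper intervention slope. The section opens by promising a comparison of improvement across arms. In a growth curve model with time at level 1 and arm at level 2, that comparison ordinarily means arm predicting the time slope. On this view the interaction is implied, the full equation can be left to an analysis plan, and the first half is a slip of wording. The percentages, moreover, come from variances that the documents do not give, ignore site clustering, and describe a rule that is not the one attached to H1.

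Much of this stands. A reader might infer from the main-effects clause that H1 could be declared supported when both arms improve equally. The document does not support that reading: equal improvement meets the slope criterion only at the nominal error rate. A reader might also infer that a true effect would be missed if the intervention arm started lower. That would require positive main effects to be necessary for H1, and the text does not say they are.

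Two things survive. The first clause is an incorrect statement, not an omitted detail, and it concerns the very comparison the analysis sets out to make. The interaction may be implied by convention, but the text names only time and arm and then speaks of main effects, which points to the additive model. H1's wording as a difference in level gives that reading further room.

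**Conclusion.** The clause is wrong as written: positive main effects of time and arm are neither sufficient for differential improvement nor needed for it. Beside it stands a correct slope criterion for H1, but the listed predictors do not contain the term that would test it. The defect is an internal inconsistency in the rule for the trial's planned hypothesis test. It is not a demonstrated inflation of the error rate for H1.

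This conclusion is algebraic and rests on no assumed variance. The size of the problem for anyone who relies on the main-effects reading is illustrative only: about 19% to 98% for arm gaps of 0.3 to 0.8 across two assumed variance sets, with no site clustering. The contrast with the slope test at about 2.5% does not depend on the variances chosen; the individual percentages do. The point should be corrected before the phase 3 data are analysed.

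**What to change.** - Delete the clause on main effects.
- Add the cross-level time-by-arm interaction to the growth model, with time coded to match the stated contrast of baseline and performance periods. With a period indicator, the coefficient is the between-arm difference in change from baseline; with monthly time, it must isolate the change in the performance period.
- State that, in the model for each coordination composite, this coefficient is the sole test of H1 at the two-sided 0.05 already given under Participants.
- State that the arm main effect is not interpreted as an intervention effect.
- Align the wording of H1 in Objectives with greater improvement, so that it matches the test.

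The cost is a few sentences. No new data are needed, and Trial status describes phase 3 as still in preparation.
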